## Methods

### Reporting Guidelines

This protocol is reported in accordance with the Guidance for Reporting Involvement of Patients and the Public–Short Form (GRIPP2-SF) checklist [25] and the SPIRIT 2025 (Standard Protocol Items: Recommendations for Interventional Trials) guidelines (See Checklist 1 and Checklist 2).

### Intervention

Following development conducted in phase 1 of the project, the ASLEEP intervention will consist of 2 courses. The basic course has been developed to promote good sleep in a broad group of adults aged 50 years and older ([name]; [name], PhD; [name]; et al; unpublished data; November 2025) and starts off with a video providing instructions on how to complete the digital sleep diary. Participants will then complete a 7-day sleep diary. After completion of the sleep diary, 3 educational modules will be unlocked and delivered through short videos (see Table 1 for video descriptions) focusing on healthy sleep and sleep habits. Then, feedback reports based on recorded sleep through the sleep diary will be made available to participants, with a focus on sleep efficiency. Findings from the acceptability and feasibility study ([name]; [name], PhD; [name]; et al; unpublished data; November 2025) showed that the basic course content was well accepted, with participants describing the videos as clear, systematic, appropriately lengthy, and helpful for understanding sleep and their own sleep patterns. Several participants appreciated the expert-led dialogue format of the videos. The sleep diary was also viewed as meaningful, increasing awareness of sleep habits and prompting daily reflection on factors affecting sleep.

**Table 1. T1:** Video descriptions.

Video (length)	Name	Description
Sleep diary instruction (17 min 17 s)	An instruction to keeping digital sleep diary	This video provides step-by-step instructions on how to keep a sleep diary, along with clarification of common misunderstandings people may have when logging their sleep.
Video module 1 (20 min 3 s)	What is sleep and how it is regulated	This video explains what sleep is, its role in the body, and the biological processes that govern it.
Video module 2 (18 min 10 s)	Assessing poor sleep	This video addresses how poor sleep can be assessed, discusses its possible causes, approaches to diagnosis, and provides a general overview of different sleep disorders.
Video module 3 (30 min 10 s)	Treatment of insomnia	This video module focuses on the management of insomnia, including definitions, prevalence, and treatment strategies for both short-term and chronic insomnia, as well as principles of sleep regulation. Additionally, [name] gives sleep hygiene advice, discussing ways to maintain sufficient sleep, support a healthy circadian rhythm, and minimize evening and nighttime arousal through habits and behavioral practices.

As part of phase 1 of the project, the ASLEEP advanced course will be developed and subsequently offered to participants in a fully digital RCT to assess its effect on sleep outcomes. Eligible participants who have completed the basic course will be funneled into the advanced course if their post–basic course score on the ISI [25] is 10 or higher (defined as symptoms of insomnia) [26].

The advanced course will be developed according to established protocol for CBT-I, drawing on core components such as sleep restriction, stimulus control, cognitive restructuring, sleep-hygiene reinforcement, and relapse prevention [27]. However, unlike other existing digital CBT-I programs (eg, SHUTi, Sleepio), which deliver these components within a single treatment stream, ASLEEP applies a stepped-care approach [28] in which only participants who continue to report insomnia symptoms after completing the basic course progress to the more treatment-intensive modules. The ASLEEP advanced course is expected to consist of a series of weekly digital modules delivered over approximately 6 weeks, although the exact number and pacing of modules will be finalized during the development phase. Consistent with evidence identifying sleep restriction and stimulus control as the most effective components of CBT-I [29], these components will constitute the core of the intervention. Sleep restriction aims to consolidate sleep and strengthen homeostatic sleep pressure by limiting time in bed to approximate actual sleep duration and gradually expanding it as sleep becomes more efficient [28]. Stimulus control complements this by re-establishing the bed and bedroom as cues for sleep rather than wakefulness through structured behavioral instructions, including going to bed only when sleepy, leaving the bed if unable to sleep, and maintaining consistent rise times.

A sleep diary will be completed throughout the advanced course to track progress and to tailor individual intervention recommendations, including ongoing adjustment of the sleep-restriction schedule.

### Phase 1: ASLEEP Development, Implementation, and Integration

The ASLEEP project is guided by the updated Medical Research Council (MRC) framework for the development and evaluation of complex interventions, which emphasizes an iterative process integrating development, feasibility testing, evaluation, and implementation, supported by ongoing consideration of context, program theory, stakeholder engagement, and economic factors [30]. In line with this framework, we have already developed (phase 1 of the MRC framework) and assessed the acceptability of the basic course and the feasibility of delivering ASLEEP through the PROTECT Norge infrastructure (phase 2 of the MRC framework) ([name]; [name], PhD; [name]; et al; unpublished data; November 2025), and we are moving on to the next phases of development and evaluation.

Building on the findings from the acceptability and feasibility study showing that some participants missed the opportunity to use their own devices rather than a study-provided iPad ([name]; [name], PhD; [name]; et al; unpublished data; November 2025), the user interface will be optimized to support access across devices, including smartphones, tablets, and personal computers, via both a mobile app or a web browser. This process will be informed by human-centered design to ensure user and stakeholder engagement in the development process. While the MRC framework provides overarching guidance for complex intervention development and evaluation, design thinking adds a complementary methodological perspective to the development phase of the project.

Integration of the ASLEEP study, including registration, consenting and screening, web page text, study documents, and new questionnaires on the PROTECT Norge infrastructure, will undergo multiple rounds of user acceptance testing (UAT) in a process described in a previous publication.

As part of the implementation work, a dialogue with the Western Regional Health Authority digitalization department has been initiated to discuss technical compatibility and potentially building on existing regional digital health infrastructures, thereby supporting potential future integration into existing health care pathways and real-world deployment.

### Phase 2: Short- and Long-Term Evaluation of ASLEEP

#### RCT Design

This study will be an RCT nested within the cohort of PROTECT Norge, a 10-year digital follow-up study with annual data collection since the start in 2020. The treatment arm will be compared with a waitlist control group. Screening, recruitment, and data collection will be conducted through the PROTECT platform. This RCT will be registered in ClinicalTrials.gov.

### Comparison Group

Eligible participants that are not randomized to the intervention will go into a waitlist control group and will receive access to the intervention after a predetermined delay.

### Recruitment

Participants will be recruited from the PROTECT Norge cohort among individuals who have provided consent for contact regarding future studies. A general invitation will be sent to the whole cohort to perform the basic (tier 1) ASLEEP course. Subsequent scoring of the ISI [26] score and the Global Sleep Assessment Questionnaire [31] will be used to evaluate eligibility for the advanced (tier 2) ASLEEP course and hence the RCT (see further details below).

### Eligibility Criteria

Inclusion criteria are as follows: participants must have completed the ASLEEP basic course, have an ISI score of 10 or higher, and have an insomnia duration exceeding 3 months.

Exclusion criteria are as follows: participants with insomnia symptoms that stem from other sleep disorders, including obstructive sleep apnea, restless legs syndrome, parasomnias, and hypersomnia, will be screened for based on selected items (Q2, Q6, Q7, and Q9) from the Global Sleep Assessment Questionnaire [32].

### Randomization and Masking

Participants will be randomized in a 1:1 ratio to either the intervention group or the waitlist control group using simple block randomization with varying block sizes of 6 to 10 participants. The allocation sequence will be computer generated in advance by a member of the research team not involved in participant recruitment or follow-up.

Randomization will be performed after completion of baseline assessments and confirmation of eligibility. Allocation will be implemented manually by authorized PROTECT Norge study staff using the pregenerated allocation sequence. Based on group assignment, participants will be provided with a personal access code to be entered on the PROTECT Norge study website. Entry of the code triggers the predefined scheduling of study activities within the platform.

Members of the research team involved in data analysis will be blinded to group allocation until the inferential analyses of the primary 3-month outcomes have been finalized. Study staff with direct participant contact through the PROTECT Norge help desk will not take part in data analysis.

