**Methods:**

The project will be conducted in 2 phases. Phase 1 focuses on refining and optimizing ASLEEP, developing an advanced CBT-I course, and integrating a nested trial into PROTECT (Platform for Research Online to investigate Cognition and Genetics in Ageing) Norge, a fully automated digital research platform. Phase 2 is a fully digital, 2-arm, waitlist-controlled randomized controlled trial, with 400 participants randomized 1:1 to the intervention or waitlist control and allocation stratified by age and insomnia severity. Outcomes will be assessed at baseline and at 3, 6, and 12 months, with a 15-month follow-up for the waitlist group. The primary outcome is insomnia severity measured by the Insomnia Severity Index. Secondary outcomes include sleep medication use, depression, anxiety, and cognition.

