### Ethical Considerations

This project will be conducted in accordance with the Declaration of Helsinki [35] and complies with the General Data Protection Regulation (GDPR, 2018) and Stavanger University Hospital’s data security policy.

The ASLEEP RCT will be conducted as a nested study within the PROTECT Norge infrastructure, which was launched in 2020 and approved by the Regional Committee for Medical and Health Research Ethics, West (REK vest, reference 2019/478). A separate application for ethical approval for the ASLEEP project will be submitted to REK, and internal approval will be sought at Stavanger University Hospital, including a data protection impact assessment for any new technology used to process participant data. Only participants who have previously provided broad consent (C4C) for future studies within PROTECT Norge will be invited, and all will provide additional written informed consent specific to the ASLEEP RCT study through a secure and validated procedure. Participation is voluntary, and participants may withdraw from the study at any time, without giving a reason. No financial compensation will be provided for participation.

All study data will be stored on secure cloud servers in Norway, with regular backups and monthly data transfers from the PROTECT Norge infrastructure to internal servers at Stavanger University Hospital. Any significant protocol modifications (eg, changes to eligibility criteria, outcomes, or analyses) will be submitted for review by the REK, updated in the trial registry and appropriate internal registries at Stavanger University Hospital. Personally identifiable information will be stored separately from research data, and data will be retained for 10 years following study completion and then permanently anonymized by deleting the reidentification key. Access to personally identifiable information will be restricted to authorized research personnel only.

Specifically for the phase 2 RCT, access to identifiable data will be restricted to authorized study staff with direct participant contact through the PROTECT Norge help desk via a secure, access-controlled management portal requiring authenticated login. Pseudonymized datasets will be used for data analysis by members of the research team involved in data analysis. Study staff responsible for system administration, participant support, and adherence monitoring may have access to operational study data but will not take part in data analysis.

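### Staff who may have participant contact allocate by hand from a pregenerated sequence, and no stated safeguard keeps the next assignment hidden from them

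*Protocol article*

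**What the plan says.** The Randomization and Masking section of the protocol article sets out these steps:

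- Ratio and blocks: "Participants will be randomized in a 1:1 ratio", "using simple block randomization with varying block sizes of 6 to 10 participants".
- Generation: "The allocation sequence will be computer generated in advance by a member of the research team not involved in participant recruitment or follow-up".
- Timing: "Randomization will be performed after completion of baseline assessments and confirmation of eligibility".
- Implementation: "Allocation will be implemented manually by authorized PROTECT Norge study staff using the pregenerated allocation sequence". Each participant then receives a personal code, and entering it on the study website starts the schedule for that arm.
- Separation of roles: analysts stay blinded until the primary 3-month analysis is final, and help desk staff in contact with participants take no part in analysis.

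Three other sections bear on who the allocators are and what they can see. Ethical Considerations limits access to identifiable data in the phase 2 RCT to "authorized study staff with direct participant contact through the PROTECT Norge help desk". Intervention Fidelity has help desk staff follow study activity by hand and in real time, including whether assessments are complete. Expected Impact and Limitations give the help desk the tasks of support and reminders.

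**The concern.** Generating a sequence independently protects the trial only as long as those who apply it cannot see what comes next. Here the article fixes a manual step and gives it to study staff. It states one separation for contact staff, from analysis, and none from allocation.

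The opening is the order and timing of allocation. A general invitation goes to the whole cohort (Recruitment), so several eligible people could be waiting at once. Someone working down a list by hand could then decide who takes the next slot.

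The design makes this matter. The control is a waitlist, participants know their arm, and the primary outcome is the self-reported ISI, so randomization carries most of the protection against bias. Contact staff may form a view of who is motivated or digitally able. Limitations itself names adherence as a challenge. Selection on such traits could favour one arm without showing in the measured baseline variables.

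**Working it through.** The plan attaches no figure to allocation concealment, so there is none to reproduce. The check has two parts.

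**1. The stated safeguards against the open question**

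| Stated step | What it prevents | Does it hide the next arm from the allocator? |
|---|---|---|
| Sequence made by someone outside recruitment and follow-up | Recruiters composing the sequence | No, once staff apply it |
| Baseline and eligibility first | Baseline answers or eligibility changing after the arm is known | No; the order among eligible people stays open |
| Block sizes vary from 6 to 10 | Certain prediction at the end of a block, when only past assignments are known | Not if the list is visible |
| Contact staff kept out of analysis | Unblinded analysis | Not relevant to allocation |

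Who allocates: the allocators are authorized PROTECT Norge study staff, and they hand personal codes to individuals, which would normally need access to identity or contact details. Ethical Considerations gives that access to "authorized study staff with direct participant contact through the PROTECT Norge help desk". Overlap is therefore likely, but it is an inference.

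**2. How predictable the next assignment is**

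Assumption: blocks of 6, 8 and 10 are used equally often. The article gives only the range; a 1:1 ratio within blocks implies even sizes. Strata are ignored. The abstract mentions stratification by age and severity, but Randomization and Masking names none.

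*List visible:* 100% of next assignments are known.

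*Only past assignments known:* guess the arm that is behind, and guess at random when the arms are level. For a block of size 2m, the expected number of correct guesses is m + ½ × (2^(2m) / C(2m, m) − 1).

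- Block of 6: 3 + ½ × (64/20 − 1) = 4.10, or 68.3%
- Block of 8: 4 + ½ × (256/70 − 1) = 5.33, or 66.6%
- Block of 10: 5 + ½ × (1024/252 − 1) = 6.53, or 65.3%
- Equal use: (4.10 + 5.33 + 6.53) / 24 = 66.5%

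A simulation of 500 allocations gave 66.5% as well. Chance is 50%, and the range over any mix of these sizes is 65.3% to 68.3%.

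*Block sizes also known:* an assignment is certain once one arm in the block is used up. The expected number of certain assignments per block is 2m/(m + 1), which is 1.50, 1.60 and 1.67. The share is 4.77/24 = 19.9% (simulation: 19.7%).

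So keeping the list hidden matters more than the choice of block sizes.

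**The case against.** The strongest reply is that the text is a condensed article. Staff who apply a sequence manually need not hold the whole list: one-at-a-time release or sealed codes would fit the same words, and the full protocol may describe them. That stands. A reader might infer that allocation is unconcealed, and the article does not support this. It does, however, fix a manual procedure and spell out role separations, and none of these covers allocation. The point rests on that stated procedure.

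A reader might also infer that staff can settle doubtful eligibility cases with the next arm in view, because the exclusion concerns "participants with insomnia symptoms that stem from other sleep disorders". The documents do not support that either. The same sentence ties the screen to four items of the Global Sleep Assessment Questionnaire, Table 2 gives their scoring, and Results plans fully digital screening. No cut-off is printed, but nothing says staff adjudicate.

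Nor is baseline ISI the only adjustment. The Statistical Analysis section adds age, gender, ethnicity, marital status, education, employment, PHQ-9 and GAD-7. Some of these may relate to motivation or digital skill and would absorb part of any imbalance. What they do not capture would remain.

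Two further replies have weight. The overlap between allocators and help desk staff is inferred, since Ethical Considerations could be describing a subset of authorized staff. The motive to steer is also weakened because controls get the course after 3 months. Both lower the likelihood of a problem, but neither closes the opening.

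**Conclusion.** The point holds in a limited form. The article assigns manual allocation from a pregenerated sequence to staff who may be in contact with participants, and it states nothing that keeps the next arm from them. What is exposed is the order and timing in which already eligible people are allocated.

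Predictability is 100% if the list is visible, and about 66% if only past assignments are tracked, under the block-size assumption above. The effect on the ISI difference cannot be estimated: the documents give no basis for how often staff would steer or how different the steered participants would be. The conclusion depends on two unconfirmed conditions: that allocators can see the next entry, and that some of them have participant contact. It is a cheap improvement to the procedure. It is not evidence that the trial will be biased.

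**What to change.** Change the implementation step in Randomization and Masking so that:

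- the independent sequence generator keeps the list and releases one access code at a time;
- each release follows the logged time order in which participants became ready, and happens only after the participant's ID and confirmed eligibility are irrevocably recorded;
- help desk and recruitment staff do not see the list.

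If the platform can support it, the platform could issue the code automatically at that same point. The abstract calls PROTECT Norge "a fully automated digital research platform", but the article does not say that it can release allocations, so this has to be confirmed. Whoever holds the list should not be one of the analysts who are to stay blinded until the primary analysis is final.

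The cost is a small release log, or some configuration work in phase 1, and possibly a short delay per allocation. No extra staff are needed for the manual version, since the independent generator is already planned. The timing is good: no one has been recruited, the ethics application has not been submitted, and the trial integration has still to be built.

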### Outcome Assessment Timing

Baseline data will be obtained from all potential participants as part of the screening. At 3 months postrandomization, a similar data collection will be performed. These data will serve as the primary short-term outcome data for the study. For the waitlist group, they will also serve as an updated baseline for their intervention period, which starts immediately after they provided these data (see Textbox 1).

Textbox 1.Overview of data collection time points.

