### Statistical Analysis

Descriptive statistics will be presented for baseline demographics, including age, gender, ethnicity, marital status, education, and employment status. Counts and percentages (categorical variables) and either means and SDs (symmetric continuous variables) or medians and IQR (skewed continuous variables) will be presented for the total sample and per intervention arm. Similarly, descriptive statistics will be presented for primary and secondary outcome variables, for all time points.

The primary estimand will be the average treatment effect (ATE), defined in accordance with the International Council for Harmonisation (ICH) E9(R1) guideline on estimands and sensitivity analysis as the adjusted mean difference in insomnia symptoms measured as ISI scores between the intervention and waitlist arms at three months postbaseline. Nonadherence will be handled using the treatment policy strategy (which reflects the intention-to-treat principle under the estimand framework), meaning that the analysis will include all participants according to their randomized allocation, regardless of adherence.

The primary inferential analysis will thus be the comparison of the intervention and the waitlist arms at 3 months post baseline with regard to mean ISI scores. This comparison will be performed using analysis of covariance (ANCOVA), implemented as a linear regression model with follow-up ISI as the dependent variable, intervention arm as the independent variable, and baseline ISI as a covariate. The interaction between intervention arm and baseline ISI will be included to allow for slope heterogeneity. To improve precision, further adjustments will be made for potentially predictive baseline variables, ie, the demographic variables listed above plus baseline measures of depression (Patient Health Questionnaire-9) and anxiety (Generalized Anxiety Disorder-7). All continuous covariates will be entered linearly. The primary contrast will be reported as a marginal (population average) mean difference, obtained via model-based standardization over the joint baseline covariate distribution of the randomized sample.

The estimated ATE will be reported with a 95% CI based on a heteroscedasticity-robust SE and corresponding 2-sided *P* value. An effect size will be calculated by dividing the ATE by the pooled SD of baseline ISI scores.

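### Scheduling is triggered by a code the participant enters after allocation, with no stated route to a 3-month ISI for those who never enter it, and the primary time point has inconsistent anchors

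*Protocol article*

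**What the plan says.** The order of events is in Randomization and Masking. First, "Randomization will be performed after completion of baseline assessments and confirmation of eligibility". Then staff allocate, and "Based on group assignment, participants will be provided with a personal access code to be entered on the PROTECT Norge study website". Finally, "Entry of the code triggers the predefined scheduling of study activities within the platform". This applies to both arms. The section sets no deadline for entering the code and does not say what happens if it is never entered.

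The primary time point is described in three places. Outcome Assessment Timing says: "At 3 months postrandomization, a similar data collection will be performed". Textbox 1 defines T1 as T0 plus 3 months, with T0 being baseline. Statistical Analysis defines the estimand as a difference "between the intervention and waitlist arms at three months postbaseline" and dates the comparison from baseline a second time. Baseline itself comes before allocation: "Baseline data will be obtained from all potential participants as part of the screening".

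Statistical Analysis adopts a treatment-policy strategy, under which "the analysis will include all participants according to their randomized allocation, regardless of adherence". Missing 3-month ISI is multiply imputed from the variables of the analysis model plus 3-month PHQ-9, GAD-7 and FLAME. A delta analysis follows as a sensitivity analysis.

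**The concern.** A treatment-policy estimand needs the 3-month ISI of people who were randomised and never started. As described, collecting that score depends on a step that is itself part of starting. The people most likely to be lost are those in the intervention arm who received none of the advanced course. If they are filled in from people who did receive it, the primary estimate moves in the intervention's favour.

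The second issue is the clock. Baseline is collected at screening and randomisation comes later, so 3 months after baseline and 3 months after randomisation are different dates. If scheduling runs from code entry, there is a third. A programmer configuring the platform could not tell from the article which date starts the count.

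**Working it through.** **The plan's own figure.** Power Analysis gives 500 recruited, 20% attrition, 200 per arm analysed, effect size 0.3 and two-sided alpha 0.05. Check: 500 × 0.80 = 400. The noncentrality is 0.3 × √(200/2) = 3.0, so power is about Φ(3.0 − 1.96) = 0.851. The statement of more than 80% power is correct. If non-entry falls within the 20% allowance, power does not change. If it came on top of that allowance in both arms, an extra 5% loss leaves 190 per arm (0.832) and an extra 10% leaves 180 (0.812). Power is therefore not the main issue; bias is.

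**What the imputation can see.** The model has arm, baseline ISI, demographics, baseline PHQ-9 and GAD-7, and three auxiliaries measured at 3 months. It has no variable for code entry or adherence. The auxiliaries come from the same follow-up as the ISI, so a non-entrant with no scheduled follow-up would lack them too. The imputed score then depends on arm and baseline values, and the arm effect is learned from those observed, who are mainly starters.

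**Size of the bias.** Let δ be the effect among intervention-arm starters and f the fraction of that arm who never enter the code. Assume non-entrants have no benefit and are all unobserved.

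- True treatment-policy effect: (1−f)·δ + f·0 = (1−f)·δ
- Estimate after imputing non-entrants like starters: (1−f)·δ + f·δ = δ
- Relative overstatement: δ/[(1−f)·δ] − 1 = 1/(1−f) − 1

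The documents give no value for f. For an assumed range:

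| f | People in an intervention arm of 250 | Overstatement | True effect if δ = 0.3 SD |
|---|---|---|---|
| 5% | 12.5 | 1/0.95 − 1 = 5.3% | 0.285 |
| 10% | 25 | 1/0.90 − 1 = 11.1% | 0.270 |

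The 250 is half of the 500 in Power Analysis. The Abstract and Limitations speak of 400 randomised; with 200 per arm the counts would be 10 and 20, and the percentages would not change.

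**Which arm matters.** A waitlist participant who never enters the code gets no course before T1, and neither do the waitlist participants used to impute that score. This route therefore gives no comparable error in the waitlist arm, and the bias does not require different entry rates by arm.

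**The anchors side by side.** Outcome Assessment Timing: randomisation + 3 months. Textbox 1: baseline + 3 months. Statistical Analysis: baseline + 3 months. Randomization and Masking: scheduling triggered at code entry, with no date rule. The article states no length for the gap between baseline and randomisation or between randomisation and code entry, so the size of the discrepancy cannot be computed.

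**The case against.** A reader might infer that non-entrants are certain to go unassessed, that the 3 months run from code entry, or that the primary time point is not tied to randomisation at all. The documents do not support any of these. No section says non-entrants are left out of follow-up, and staff could contact them another way. No section says the clock starts at code entry, and a predefined schedule could use dates fixed from randomisation. Outcome Assessment Timing does name randomisation. A delay that differs by arm is plausible, since participants know their arm, but it is not documented.

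There is real mitigation. Intervention Fidelity has the help desk monitoring assessment completion in real time, and the Discussion and Limitations promise reminders and active support. Participants must have finished the basic course, including a 7-day diary, before randomisation, so non-entry may be rare. Non-starters stay in the analysis through imputation. The delta analysis shifts imputed scores arm by arm, which bears directly on this worry. It can also be said that handling of unentered codes is operational detail for the full protocol, and that platform scheduling is still to be built.

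Much of this stands, and it limits the size of the problem. But the monitoring and reminder passages do not mention unentered codes or people with no schedule. The delta analysis explores the bias and leaves the primary estimate as it was. And the point does not rest on missing detail: the article states a trigger that fits badly with its own estimand, and it states anchors that disagree.

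A reader might also infer from "Allocation will be implemented manually by authorized PROTECT Norge study staff using the pregenerated allocation sequence" that staff can see coming assignments. The text does not say how the list is held or released, so that forms no part of this point.

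**Conclusion.** The point holds in a limited form. Code entry is the only scheduling trigger described, and followed literally it can leave intervention-arm non-entrants without a 3-month ISI. The planned imputation would then treat them much like starters. The overstatement is 5.3% to 11.1% for an assumed 5% to 10% non-entry in the intervention arm, in the direction of benefit. These figures are upper values for each f: they need every non-entrant to be unobserved, to have no benefit and to be imputed with the full starter effect. Any 3-month scores the help desk recovers from non-entrants would reduce them.

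Separately, and without any assumption, the primary time point is dated from randomisation in Outcome Assessment Timing and from baseline in Textbox 1 and Statistical Analysis. This needs reconciling whatever the non-entry rate.

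Neither issue undermines the design or changes the sample size. Both are worth settling before recruitment, because outcomes not collected at 3 months may not be recoverable.

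**What to change.** 1. In Randomization and Masking, state that T1 and later assessments are scheduled from the randomisation date for every randomised participant, whether or not the code is entered, and that the code controls course access only. In the waitlist arm the later visits follow from T1, which Textbox 1 already makes the updated baseline.
2. Use months since randomisation for the primary time point in Randomization and Masking, Outcome Assessment Timing, Textbox 1 and Statistical Analysis.

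The cost is minor platform configuration, a few changes of wording, and some reminders to people who have not started. The Results section places trial integration and questionnaire scheduling still ahead within phase 1, which runs to Q4 2027, and the Abstract reports that ethics approval has not been submitted and nobody has been recruited. No change to the sample size or the primary model is needed.
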